Orsolini et al [13] also refer to this population in their more recent study, identifying *educated and informed* users within web-based drug forum communities, who can provide reliable information on psychoactive compounds. They refer to these users as *e-psychonauts*, providing the best characterization of the population to date [13]. The e-psychonauts appear to be mainly young and unmarried White males, presenting good or excellent employment conditions and with a set of key skills, including awareness to their inner *soul*; high standards of knowledge about drugs’ chemical and pharmacological issues; and high levels of both technology-related skills. They are meant to have a wide vocabulary to define their own *on drug* experiences in the most subtle and precise way possible.

Among this population, the frequency of NPS use is high, with one-third of the participants reporting its use in the last week. They view themselves as knowledgeable consumers who use the internet to accumulate information about NPS and share their own experiences, informing fellow users of potential harms. However, other studies [16] reported possible stimulant dependence (3 or more dependence symptoms) in 30% of mephedrone users. Mdege et al [8] also found that NPS users often report substance use disorder symptoms, especially craving.

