This community may have some other distinct characteristics. A minority of the sample reported that an NPS was the first drug that they had ever taken. Of those who ceased using NPS, majority found it either easy or very easy to stop. Most commonly, cessation was due to the side effects of NPS [17]. They also perceived internet forums as an important channel through which to communicate information on new drugs, and retailers reported monitoring forums to determine which drugs to stock in their store [8]. These users also tend to post online warnings based on first-hand experiences about the potential harms of the substances consumed and are willing to avoid harm to their peers. Orsolini et al [13] even stated that posting online the *on drug* experience report is arguably the *trait d’union* of all e-psychonauts, considering the intention behind using a substance is the most significant difference between a psychonaut and a typical drug user. O’Brien et al [11] also identified the role of e-psychonauts in disseminating emerging information about NPS-related harm and considered them well equipped to make a valuable contribution to NPS policy debates in general, and e-psychonauts are ideally placed to report on the effects of recent policy changes on NPS-related harms in particular.

Several authors have tried to engage cyber-psychonauts as research participants. Mdege et al [8] found difficulties in involving NPS users throughout the project due to a lack of willingness on the part of NPS users to be contacted in ways other than email. In addition, working with this population has inherent sampling problems: internet research participants are, by definition, a nonrandom and self-selecting sample, and it is very difficult to know the characteristics of the overall pool from which the sample is drawn [18,19].

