### Study Objectives and Hypothesis

The study has been designed to answer 3 main research questions:

Who are the people who first try the new substances when they emerge in the market?What are the substances emerging right now and their subjective effects?Is it possible to collect reliable data to answer these questions using a low-budget internet platform and the design used in this study?

The researchers’ initial hypotheses are as follows:

The population of e-psychonauts will be made up of functional and educated people who use drugs mainly in a recreational way.During the study period, we will be able to identify a wide variety of different substances, some of which have never been reported before in the scientific literature or by the organizations aimed at controlling illicit drug supply.The study design and implementation will attract enough research participants with sufficient commitment to provide valuable, reliable, and meaningful data to generate quality evidence.

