### Recruitment

Recruitment ads were sent to the moderators of the selected online communities after establishing bilateral communication with them, mainly to ask permission and explain the goals of the project. To maximize interest in participating in the study, the only focus was on establishing rapport with community leaders, as if they share their interest in the study, they will be able to transfer it to the rest of the community [31]. Each community moderator posted the research ad in the most appropriate way in their community after discussing it with the research team. Research ads were posted on all communities during the summer of 2019 (refer to Multimedia Appendix 3 for details). The recruitment was designed to be sequential until the designed sample size was reached or the study reached its duration limit.

The operational definition for online communities of people who use NPS has been adapted from the study by Barratt [21]:

Surface websites with at least 5 years of existencePresence of participation forums dedicated to discussing the use of NPSAt least weekly activity on the community forumThe use of pseudo-anonymity by community members to identify themselvesThe presence of official and analytical drug checking services in the community.

When the study design was completed (October 2018), there were 4 communities meeting the previously stated criteria [21]:

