As it is an exploratory study, the data analysis procedures will be mainly descriptive statistics, to maximize an adequate visualization of the data collected within the minimum space. In addition, as there is no control group, statistical tests will be limited to potential comparisons to assess bias on the results, such as comparing data from participants who complete the study with participants who drop out or are excluded. However, no statistical corrections will be applied to adjust the representativeness of the sample, as this validation will be done by comparing the sociodemographics of the study sample with the characteristics of the population of psychonauts widely reported in the literature. Statistical tests might also be used to compare information from the initial questionnaire Q1 and the data from the follow-up questionnaire Q4. The nonparametric Wilcoxon signed-rank analysis will be used to perform a mean comparison of the quantitative data and the chi-square test for qualitative data. In addition, factor analysis will be attempted to study the relationship between all the visual analog scales used to assess the subjective drug effects.

The data analysis will focus on the outcomes of the participants who completed the study. Data entries containing evident errors or inconsistent information will be discarded, and the extent to which this might have impacted the results will be reported.

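### Agreement with published psychonaut profiles cannot validate representativeness, because both samples pass through similar self-selection and some exclusions lean towards the profile in hypothesis 1

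*Protocol article*

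**What the plan says.** Under Data Management and Statistical Analysis, the article says that "no statistical corrections will be applied to adjust the representativeness of the sample, as this validation will be done by comparing the sociodemographics" of the sample with "the characteristics of the population of psychonauts widely reported in the literature". The same paragraph plans tests to look for bias, giving as its example a comparison of completers with people who drop out or are excluded. The section then says that the analysis will concentrate on those who finished the study.

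The section The e-Psychonaut Population describes the sampling problem: "internet research participants are, by definition, a nonrandom and self-selecting sample, and it is very difficult to know the characteristics of the overall pool". It also gives the published profile. The study credited with the best characterisation so far identified educated and informed "users within web-based drug forum communities, who can provide reliable information on psychoactive compounds", and reported that "The e-psychonauts appear to be mainly young and unmarried White males, presenting good or excellent employment conditions", with good technical skills and a wide vocabulary.

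Hypothesis 1, under Study Objectives and Hypothesis, is worded for the population: "The population of e-psychonauts will be made up of functional and educated people who use drugs mainly in a recreational way".

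Under Participants, an e-psychonaut is defined by recent experience with at least three new substances and by activity in online communities. Textbox 1 adds exclusions for difficulty with English, difficulty with technology, potential pregnancy and potential severe psychopathology. English and psychopathology are judged partly by the principal investigator from long written answers and platform introductions. Technology is judged by whether the candidate gets through the screening steps.

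**The concern.** The plan gives resemblance to earlier samples as its reason for making no correction, and calls that resemblance a validation. If two samples are drawn through similar channels from a population nobody has enumerated, they can agree with each other and both differ from that population.

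The first research question asks who first tries new substances, and hypothesis 1 answers it for e-psychonauts as a whole. If the study sample looks like the published profile, the plan as worded would let that be reported as evidence that the sample represents the population. Part of the agreement could instead come from who could be recruited, who passed screening and who stayed.

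**Working it through.** The plan gives no figure for representativeness, so there is none to reproduce. The check sets its statements side by side.

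1. **What the validation needs.** The comparator must describe the target population, or at least be selected differently from the study sample. Otherwise a shared bias goes unseen.
2. **What the article says of such samples.** They select themselves, and "it is very difficult to know the characteristics of the overall pool from which the sample is drawn". That statement is about internet research generally, so it covers earlier internet samples as well as this one.
3. **Where the comparator comes from.** The best published characterisation is of users of web drug forums. This study was advertised only on selected forums (Participants; Recruitment). The channels are alike.
4. **Which filters go beyond the definition.** Substance experience and forum activity define the target population, so they are not a bias in themselves. English, technology and potential severe psychopathology are additional. The last bears fairly directly on being functional. The first two, with the long written answers, bear only indirectly on education. No criterion bears on recreational use.
5. **What happens at analysis.** Concentrating on completers adds a further step of selection.
6. **What the planned bias comparison covers.** Completers against dropouts and excluded people can show selection after a candidate reaches screening. It has no data on forum users who never responded or on users of other forums.

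The mechanism can be written down, but its inputs are assumptions and appear nowhere in the documents. Let *p* be the true share with the expected profile, and *r* the chance of entering and staying for people with the profile divided by the chance for people without it. The observed share is *p·r* / (*p·r* + 1 − *p*).

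| Assumed *p* | *r* = 1 | *r* = 1.5 | *r* = 2 | *r* = 4 |
|---|---|---|---|---|
| 50% | 50% | 60% | 67% | 80% |
| 70% | 70% | 78% | 82% | 90% |

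For example, with *p* = 0.5 and *r* = 2: 1.0 / (1.0 + 0.5) = 67%. If the earlier samples had a similar *r*, they would show a similar figure, and comparing the two would not reveal *r*. The table shows only why agreement is uninformative. It does not estimate the bias in this study.

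**The case against.** The case on the other side has substance.

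- **The bias is acknowledged and partly checked.** The introduction states the self-selection problem, and the plan compares completers with dropouts and excluded people. This stands, and the fix should build on it. It does not reach selection before screening.
- **Declining to correct is defensible.** Without a known pool there is nothing to weight to. This stands. The fault lies in the reason given, not in the absence of weighting.
- **The study is exploratory and its conclusions are modest.** The article says the usefulness of the data is still unknown. That supports descriptive analysis, but it does not support the term validation.
- **The comparison can fail.** Race and marital status are not fixed by eligibility, and sex and age only in part, so disagreement would be informative. This stands. The weakness is one-sided: it concerns what agreement would show.

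A reader might also infer more than the documents support:

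- *That eligibility builds in hypothesis 1.* No criterion selects on education, employment or recreational use. The lean is partial and indirect.
- *That the group described is about 9% of candidates.* The figure 17/182 = 9.3% counts people with at least one self-administration trial. Sociodemographic data come from Q1, which is completed after acceptance and before any trial, and the number who completed Q1 is not given.
- *That a specific inflation of the profile can be stated.* Any such number needs retention rates by profile, which the documents do not contain.
- *That the age change, the pregnancy exclusion or the drug-checking requirement biases hypothesis 1.* "Research ads were posted on all communities during the summer of 2019", and the amendment lowering the minimum age from 21 to 18 was submitted in November 2019. But age is not part of hypothesis 1, and the number who entered under the old limit is not given. Neither of the other two has a stated link to being functional, educated or a recreational user.

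**Conclusion.** The point holds as a matter of inference and scope. Agreement with the literature cannot validate representativeness on the protocol's own description of its samples, and some exclusions, together with the focus on completers, may move the sample towards the expected profile. The direction is plausible for the functional part of hypothesis 1, weaker for the educated part, and unsupported for the recreational part. The size cannot be determined from the documents.

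The conclusion rests on two assumptions. The first is that the comparator samples were self-selected in a similar way; this follows from the article's general statement and its forum-based description, since the cited studies were not available. The second is that the population wording of hypothesis 1 is meant as written. The documents do not support the stronger claim that hypothesis 1 is confirmed by design. What changes is how far the answer to the first research question can be generalised.

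**What to change.** - Call the literature comparison descriptive and remove the claim that it validates representativeness. Keep the decision not to weight, and give the unknown source pool as the reason.
- Describe hypothesis 1 on all accepted participants with a valid Q1, rather than mainly on completers.
- Extend the planned bias comparison to a table by stage: screened, accepted, at least one self-administration trial, one year. Give the reasons for exclusion. Use Q1 from acceptance onwards, and for those screened whichever variables Q0 holds. Q0's items are not listed in the article, so it may lack education or employment. Data of participants removed for severe violations were deleted, so that group may be available only as a count, if at all.
- Limit the conclusion to English-speaking users of the selected forums without evident severe psychopathology, and say that selection by forum and by volunteering could not be assessed.

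The cost is one more table and a narrower claim. No new data collection is needed.

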### Sample Size

In the most recent review consulted by the authors, the sample sizes reached with web-based questionnaires in people who use illicit drugs ranged from 80 to 9867 [36]. The expected losses while filling these types of questionnaires are about 50% of the sample, but the authors have not found other online longitudinal studies including questionnaires like this one. According to the aforementioned review, the authors expected 80 candidates as the best possible estimate to achieve 40 final participants. Assuming that each participant takes one NPS every month during the duration of the study, the expected number of registered self-administration trials of NPS would be 480. As the study has been designed as exploratory, the sample size could not be determined based on the needs to perform specific statistical tests.

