The first mandatory step was to fill a sociodemographic and drug use history questionnaire (Q1). This questionnaire was available to each participant through a participant-specific link, which was sent by email once they were accepted. After that, participants were asked to fill the sample submission questionnaire (Q2), where information about the sample they intended to consume was asked. This questionnaire was then reviewed by the principal investigator and approved if the substance met the study criteria of being a new psychoactive substance. The samples that did not meet the inclusion criteria were not accepted, and the participant was notified by email. The sample submission questionnaire (Q2) was available to all accepted participants as a link on the platform. All the questionnaire answers were reviewed weekly by a member of the research team to communicate to the participant the acceptance of the sample and to mark them as valid or invalid data for later analysis.

If the sample was approved, the participant received a specifically generated sample code with the instructions to send a small amount of the sample (approximately 30 mg, usually below the psychoactive threshold) via traditional mail to the laboratory at the IMIM. The sample was analyzed there, and the result was sent back to the user, along with harm reduction advice when appropriate.

Meanwhile, the users could consume the substance whenever they decided, as the study was intended to be observational. However, most of the participants waited until they had the result of the laboratory analysis to proceed with the self-administration trial. The self-administration trial started with the users filling the drug effect baseline questionnaire (Q3a), and then, they consumed the reported substance and filled the drug effect questionnaire (Q3b) 24 hours after filling the baseline questionnaire (Q3a). The links to these questionnaires were available for all participants in the forum, and the veracity of the information was ensured by asking information only available to each participant, such as the sample code of the reported sample.

Study recruitment began in August 2019 and is still ongoing. In August 2020, the first participant concluded the 1-year follow-up.

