## Results

The research protocol was approved by the IRB of the *IMIM* on December 11, 2018. Data collection started in August 2019 and was still ongoing when the protocol was submitted (September 2020), finalizing in October 2020.

Data analysis began in November 2020, and it is still ongoing. The authors expect to submit the first manuscript with preliminary results by the end of 2021.

From a total of 182 screened candidates, only 17 (9.3%) completed at least one self-administration trial, resulting in a total number of 64 self-administration trials. From these, 40 different substances were analyzed.

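### The two named tests do not cover both a paired and an unpaired comparison: chi-square ignores the pairing of Q1–Q4 answers, and signed-rank has no pairs for completers versus dropouts

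*Protocol article*

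**What the plan says.** The Data Management and Statistical Analysis section describes an exploratory, mainly descriptive analysis without a control group, in which tests have a limited place. It mentions two uses.

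- A check for bias, for example by "comparing data from participants who complete the study with participants who drop out or are excluded".
- A possible before–after analysis: "Statistical tests might also be used to compare information from the initial questionnaire Q1 and the data from the follow-up questionnaire Q4".

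The next sentence gives the tests: "The nonparametric Wilcoxon signed-rank analysis will be used to perform a mean comparison of the quantitative data and the chi-square test for qualitative data". It does not tie either test to either comparison. The article names no rank-sum test, no McNemar test and no other paired categorical test.

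Under Study Procedures and Timeline, Q1 is tied to the individual: "This questionnaire was available to each participant through a participant-specific link". Under Data Collection, Q4 is the 1-year follow-up questionnaire. Under Sample Size, "the authors expected 80 candidates as the best possible estimate to achieve 40 final participants", and the article adds that "the sample size could not be determined based on the needs to perform specific statistical tests".

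**The concern.** The two comparisons differ in structure. Completers and dropouts are different people, so the groups are independent. Q1 and Q4 come from the same people a year apart, so the answers are paired and can be linked. One quantitative test and one categorical test cannot serve both structures, yet only one of each is named.

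This is not detail left to a fuller document: the article names the tests. Two results are at stake. One is the categorical part of the one-year change, where ignoring the pairing discards information. The other, if the sentence reaches that far, is the quantitative part of the attrition check, where the named test cannot be applied. That check matters because the analysis focuses on people who complete the study, and no statistical correction for representativeness is planned.

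**Working it through.** **Planning figures.** With 50% loss, 40 / (1 − 0.5) = 80 candidates, as stated. One substance a month for a year gives 40 × 12 = 480 trials, as stated ("the expected number of registered self-administration trials of NPS would be 480"). Both reproduce. The point does not depend on them, except that 40 serves below as the planned number of people.

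**Which test fits which comparison.**

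| | Quantitative: signed-rank named | Categorical: chi-square named |
|---|---|---|
| Q1 vs Q4 (paired) | fits | ignores the pairing |
| Completers vs dropouts or excluded (unpaired) | no pairs exist | fits |

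The test sentence can be read in three ways:

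1. It covers both comparisons: two of the four cells are wrong.
2. It covers only Q1–Q4, the sentence just before it: chi-square is wrong.
3. It covers only completers versus dropouts: signed-rank is wrong.

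No reading is free of a mismatch. Under all three, signed-rank is misdescribed, since it tests whether within-person differences are centred on zero using their signed ranks, not whether two means are equal.

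**Signed-rank without pairs.** With groups of unequal size the statistic cannot be formed. With two simulated unpaired groups of 40, the p-value depended on an arbitrary pairing: 0.004 to 0.28 over 2,000 pairings of the same data, against a single rank-sum p-value of 0.077.

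**Chi-square on paired answers.** These inputs are assumptions, not in the documents: a yes/no item, within-person correlation r, two-sided 0.05, and the answers stacked as a time-by-answer table.

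*No change, 50% at both times.* The true variance of the difference in proportions is 2p(1 − p)(1 − r)/n. Pearson chi-square uses 2p(1 − p)/n. The test statistic is therefore too small, and the actual two-sided error is about P(|Z| > 1.96/√(1 − r)). For r = 0.5, 1.96/√0.5 = 2.77, which gives about 0.6%. Simulation (50,000 data sets, n = 40):

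| r | Stacked chi-square | McNemar, asymptotic |
|---|---|---|
| 0.3 | 2.3% | 4.7% |
| 0.5 | 0.8% | 4.4% |
| 0.7 | 0.07% | 4.8% |

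*True change from 50% to 70%, r = 0.5, n = 40.*

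- P(yes, yes) = 0.5 × 0.7 + 0.5 × √(0.25 × 0.21) = 0.465.
- Discordant probabilities: 0.5 − 0.465 = 0.035 and 0.7 − 0.465 = 0.235, total 0.271.
- True standard error of the difference: √((0.271 − 0.2²)/40) = 0.076.
- Chi-square needs a difference above 1.96 × √(2 × 0.6 × 0.4/40) = 0.215. Power ≈ Φ((0.2 − 0.215)/0.076) ≈ 42%.
- McNemar needs about 1.96 × √(0.271/40) = 0.161. Power ≈ Φ((0.2 − 0.161)/0.076) ≈ 69%.

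Simulation, which does not rely on these normal approximations, gives 44% for stacked chi-square, 73% for asymptotic McNemar and 63% for exact McNemar.

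*One concrete table.* Of 40 people, 20 say yes at Q1 and 28 at Q4; 9 change to yes and 1 changes to no. Stacked chi-square: 80 × (20 × 12 − 20 × 28)² / (40 × 40 × 48 × 32) = 3.33, p = 0.068. McNemar: (9 − 1)²/10 = 6.4, p = 0.011; exact McNemar p = 0.021.

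*Small numbers.* At an illustrative n = 17 with the same assumptions, power is 15% for stacked chi-square, 36% for asymptotic McNemar and 13% for exact McNemar. The exact version gives no gain there.

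**The case against.** The strongest reply is that the sentence may belong only to Q1–Q4. It follows that comparison directly, and signed-rank is a paired test. On that reading the bias check merely has no named test, which a condensed article may leave to a fuller document. That is fair, and it means the unpaired half of the point is conditional. The chi-square mismatch remains. Chi-square might be loose shorthand for McNemar's chi-square, but the text does not say so, and McNemar would not fit the unpaired comparison.

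Three stronger readings are tempting and are not supported:

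- *That every inferential result is invalid.* Two of the four cells are correctly served.
- *That the attrition check is a comparison of 17 with 165 people, with a power to match.* The Results say "From a total of 182 screened candidates, only 17 (9.3%) completed at least one self-administration trial". Those 17 are not stated to be one-year completers or people with both Q1 and Q4. The other 182 − 17 = 165 are not stated to be dropouts; they can include candidates rejected at screening, and Q1 went only to accepted participants. The article gives no counts of completers, dropouts or Q4 responses.
- *That chi-square would flood the report with spurious change.* That would need a Q1-by-Q4 cross-table, where Pearson chi-square tests association rather than change. The plan proposes no such table. On the stacked table the test is conservative, so the cost is lost power.

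It is also true that the tests are optional and that the main outcome, the Q3b minus Q3a difference on the visual analogue scales, is not one of these two comparisons.

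**Conclusion.** The point stands as a wrongly specified rule of modest severity. One named test does not fit under either single-comparison reading, and two cells are mismatched if the sentence covers both. The description of signed-rank as a comparison of means is wrong in every case.

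For categorical Q1–Q4 items, the size at the planned 40 people is an actual error rate under 1% instead of 5%, and about 44% power where asymptotic McNemar has about 73%. These figures rest on assumed values: correlation 0.5, a 50% to 70% change and two-sided 0.05. The loss shrinks as the within-person correlation falls and disappears near zero. The structural mismatch depends on none of these assumptions.

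Severity stays modest because the study is exploratory and mainly descriptive, the tests are only potential, and the sample was not sized for any test.

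**What to change.** Replace the test sentence with a short paragraph that assigns tests by comparison and data type:

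- **Q1 versus Q4, same participants.** Quantitative items: Wilcoxon signed-rank, described as a test of within-person change and not of means. Binary items: McNemar, asymptotic or mid-p, since the exact version is very conservative at small numbers. Items with more than two categories: Stuart–Maxwell or Bowker.
- **Completers versus dropouts or excluded.** Quantitative items: Wilcoxon rank-sum (Mann–Whitney). Categorical items: chi-square, or Fisher's exact test where expected counts are small.

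The cost is one paragraph. The tests are standard and can be run in R, which the plan already uses. No new data are needed.

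### The plan names one test per data type without tying it to a comparison, so on either reading of the sentence a named test does not match its design

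*Protocol article*

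**What the plan says.** All of this stands in the protocol article under Data Management and Statistical Analysis. The analysis is to be mainly descriptive. Because there is no control group, "statistical tests will be limited to potential comparisons to assess bias on the results", and the example given is "comparing data from participants who complete the study with participants who drop out or are excluded". After a sentence on representativeness, a second use is added: "Statistical tests might also be used to compare information from the initial questionnaire Q1 and the data from the follow-up questionnaire Q4".

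The next sentence names the tests. For quantitative items, "The nonparametric Wilcoxon signed-rank analysis will be used to perform a mean comparison of the quantitative data"; for categorical items it continues "and the chi-square test for qualitative data". Neither test is tied to one of the two comparisons. No unpaired test for quantitative data is named anywhere in the article, and no paired test for categorical data.

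**The concern.** The two comparisons have different designs. Completers and the people lost or excluded are separate individuals, so they form independent groups. Q1 and Q4 are answered by the same participant about a year apart, so those data are paired. The signed-rank test is a paired (or one-sample) test. The ordinary chi-square test is for independent observations. A sentence that gives one of each, sorted by data type rather than by design, cannot suit both comparisons.

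At stake is the example the plan itself gives of a formal check for bias. The same section says that the analysis will concentrate on those who completed and that no statistical correction for representativeness will be made, so the check should be specified correctly. The article also has an independent statistician analysing the same data in R, in parallel with the team's own Excel analysis. Two analysts working from this sentence could reasonably choose different tests.

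**Working it through.** **The article's own figures.** Under Sample Size, "The expected losses while filling these types of questionnaires are about 50% of the sample", and "the authors expected 80 candidates as the best possible estimate to achieve 40 final participants": 40 / (1 − 0.5) = 80, which reproduces. Under Results, "From a total of 182 screened candidates, only 17 (9.3%) completed at least one self-administration trial": 17 / 182 = 0.093, which also reproduces. These figures are background only. The point is a match of test to design and depends on none of them.

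**What each test needs.**

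- Signed-rank: for each person *i*, a difference D_i = Y_i − X_i. The statistic is the sum of the ranks of |D_i| over those with D_i > 0. Without two values on the same person there is no D_i. The one-sample form does not compare two groups either.
- Rank-sum (Mann-Whitney): the number of cross-group pairs (*i*, *j*) with X_i > Y_j, counting ties as one half. It is defined for any two independent groups, whatever their sizes.
- Ordinary chi-square: compares answer frequencies between independent observations. If *n* people answer at Q1 and again at Q4, stacking the answers treats 2*n* correlated responses as independent. Cross-tabulating Q1 against Q4 instead tests whether the answers are associated, not whether they have changed.
- McNemar (binary item): (b − c)² / (b + c), where *b* and *c* count the people who changed in each direction. This uses the pairing.

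**The named tests set against the designs.**

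| Comparison | Data | Design | Suitable test | Sentence read as covering both comparisons | Sentence read as covering Q1–Q4 only |
|---|---|---|---|---|---|
| Completers vs dropouts or excluded | quantitative | independent | rank-sum | signed-rank: mismatch | none named |
| Completers vs dropouts or excluded | categorical | independent | chi-square or Fisher's exact | chi-square: fits | none named |
| Q1 vs Q4 | quantitative | paired | signed-rank | signed-rank: fits | signed-rank: fits |
| Q1 vs Q4 | categorical | paired | McNemar or extension | chi-square: mismatch | chi-square: mismatch |

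The broad reading gives two mismatches. The narrow reading gives one, and leaves the bias check without a named test. No reading makes every stated test correct.

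**Wording.** The sentence calls the signed-rank analysis a comparison of means. It tests whether the paired differences are centred symmetrically on zero; it does not compare two means.

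**Why no numerical effect is given.** That would need the numbers of completers and of dropouts or excluded people with usable data. The article does not give them. The 17 in Results are people with at least one self-administration trial, not people who finished the study. The remainder, 182 − 17 = 165, are all other screened candidates. Under Study Procedures and Timeline, Q1 was sent only after acceptance, so candidates rejected at screening have no Q1, and only complete and valid questionnaires are to be analysed.

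**The case against.** The strongest reply is that the sentence naming the tests directly follows the one about Q1 and Q4, while the completer example stands further back, with the sentence on representativeness between them. Read with its neighbour, the signed-rank test is right. The silence on the bias check would then be a detail that an article may leave to the full protocol or analysis plan. This stands in part: nobody can say for certain that the authors meant signed-rank for the completer check, and silence alone would not be a finding. It does not clear the sentence, because the same reading applies the ordinary chi-square to paired answers. That is a stated choice, and it does not fit.

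A second reply is that a competent statistician would see the mismatch and substitute the right test. That is likely, and it limits the harm.

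A reader might infer something stronger: that the bias check would be run on arbitrary pairs of strangers, with a p-value that depends on row order and most of the larger group discarded. The documents do not support this. They plan no such pairing, and with unequal groups a paired test simply has no pairs to run on. A reader might also take 17 against 165 as the completer and dropout groups and derive a loss of power. As shown above, those are not the groups in question.

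**Conclusion.** The point holds as a mismatch between the named tests and the designs they are to serve. It rests on two facts in the text, namely that the tests are assigned by data type alone and that one comparison is between people and the other within people. It needs no assumption about effect size, variance or group size. What cannot be said is which of the two readings the authors intended.

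The consequence is modest. The study is described as exploratory, the comparisons as potential ones, and the completer check as an example. The main outcome, the change in visual analog scale score from Q3a to Q3b, does not depend on it. The correction is still worth making, because it costs almost nothing and settles how the plan's own example of a bias test is to be done.

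**What to change.** Replace the single sentence by two, one per comparison.

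- **Completers against those who drop out or are excluded:** Wilcoxon rank-sum (Mann-Whitney) test for quantitative items; chi-square test for categorical items, or Fisher's exact test where counts are small.
- **Q1 against Q4 in the same participants:** Wilcoxon signed-rank test for quantitative items; McNemar's test for binary items, or an extension of it for items with more than two categories.

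Drop the description of the rank tests as comparing means.

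The cost is one sentence rewritten as two and a small change to the R code: the paired or unpaired option of the Wilcoxon call, and a McNemar call for the paired categorical items. No new data are needed, and no sample-size figure changes.
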